[figure not shown]

## 1. Administrative information

### 1.1 Trial Registration

To be submitted to the Australian and New Zealand Clinical Trials Registry upon Human Research Ethics Committee approval

### 1.2 Funding

New South Wales Department of Health

#### **Committees**

Three committees will guide the project- a project executive will oversee all aspects of the project, a working group will be responsible for the day-to-day operational activities, and an external advisory group will provide expert advice. An organisational diagram and terms of reference for each of these groups are attached in Appendix 1.

#### 1.4 Glossary of abbreviations and terms

|        |                                                    |
|--------|----------------------------------------------------|
| ACCHS  | Aboriginal Community Controlled Health Service     |
| ACI    | Agency for Clinical Innovation                     |
| AH&MRC | NSW Aboriginal Health and Medical Research Council |
| CAH    | Centre for Aboriginal Health, NSW Health           |
| CPH    | Centre for Population Health, NSW Health           |
| CI     | Cancer Institute NSW                               |
| CQI    | Continuous Quality Improvement                     |
| MSHR   | Menzies School of Health Research, Darwin          |
| TGI    | The George Institute for Global Health             |

## 2. Protocol Synopsis

### Background

Although there have been recent encouraging declines in smoking cessation, in 2012-13, 41% of Aboriginal and Torres Strait Islander people over the age of 15 smoked cigarettes daily – over two times greater than the general population. The personal and societal impact of smoking-related diseases is inequitably distributed with, for example, Aboriginal and Torres Strait Islander peoples experiencing around five times greater cardiovascular disease burden than other Australians. Mobile health technologies are emerging as a cost-effective strategy to lower smoking rates but to date no such trials have been conducted in Australia.

### Study design

A single blinded, pilot, randomised, controlled trial involving approximately 200 Aboriginal smokers with an average follow-up of 6 months.

### Intervention

- (1) A multifaceted smartphone application available on Android or iOS platforms that comprises a personalised profile and quit plan, behavioural strategies to increase motivation to quit and maintain an quit attempt, craving support, and a challenge feature in which users can 'compete' with others on a personalised challenge.
- (2) Usual smoking cessation support provided through either the participating Aboriginal Community Controlled Health Service or the NSW Aboriginal Quitline.

### Aims

We hypothesise that a multi-faceted intervention using a mobile phone application when combined with usual smoking cessation support services will double smoking abstinence rates at 6 months.

### Patient eligibility

Consenting Aboriginal people (aged >16 years) with access to an Android or iOS phone who are willing to make a quit attempt in the next month.

### Randomisation

Centrally performed web-based 1:1 allocation to the intervention versus usual smoking cessation services using a permuted block sequence stratified by study centre, gender and age (Figure 1)

### Data collection

Data will be collected via telephone assessments at baseline, 4 weeks and 6 months by a project officer who is blinded to group allocation.

### Primary Outcome

The primary outcome is self-reported continuous smoking abstinence, objectively verified at 6 months. Self-reported continuous abstinence is defined as no more than five cigarettes smoked in the past week at 4 weeks follow-up and no more than five cigarettes smoked since the start of the abstinence period at 6 months of follow-up. Self-reported smoking cessation will be confirmed with an Airmet Scientific Micro Plus Smokerlyzer (carbon monoxide metre breath test where a reading of >8 represents recent tobacco smoking). (10)

### Secondary Outcomes

Secondary outcomes are point prevalence of abstinence (ie, no smoking in the past 7 days) at 4 weeks and 6 months, and self-reported continuous abstinence since the start of the abstinence period, 28-day abstinence, and use of other smoking cessation services (counselling, nicotine replacement therapy, medication) during the trial.

Feasibility and acceptability data will also be collected through surveys and usage analytics of the phone application.

### Statistical power

Based on previous studies the abstinence rate is assumed to be double that of the control arm. 1000 participants would be needed to detect a 5% absolute difference (ie: 10.0% vs 5.0%; relative risk 2.00), assuming a 15% loss to follow-up,  $\alpha=0.05$  and 80% probability of detecting a significant difference with p values  $<0.05$  judged as significant. This study will be a pilot RCT in which 200 participants will be recruited to assess feasibility, resource considerations, acceptability and preliminary effectiveness data to inform a future, adequately powered trial.

Using the secondary outcome measure of 7-day abstinence rates at 4 weeks, and assuming the control arm abstinence rate is 12% and the intervention arm abstinence rate is 2.4 times greater (as observed in previous studies), there will be 80% probability of detecting a significant difference with 200 participants from the pilot study.

### Significance

There have been no controlled trials of mobile health strategies for smoking cessation in Australia and only one trial worldwide involving Indigenous populations. If the outcomes provide sufficient justification for a fully powered trial, it could make a major contribution on effective, scalable and cheap strategies to lower smoking related disease burden in Aboriginal communities.

**Figure 1: Study Schema**

[figure not shown]

### 3. Introduction

#### 3.1 Background

Despite Australia having one of the lowest rates of smoking in the world, Aboriginal and Torres Strait Islander people are more than twice as likely to smoke as other Australians. Although there have been recent encouraging declines in smoking cessation, in 2012-13, 41% of Aboriginal and Torres Strait Islander people over the age of 15 smoked cigarettes daily.(1) A recent national survey found that although Aboriginal and Torres Strait Islander smokers are less successful at quitting, they are more likely to have made a quit attempt in the last year than non-Aboriginal smokers (MJA in press). Smoking affects whole households with 62% of households with Aboriginal and Torres Strait Islander residents having a least one regular smoker.(2) The personal and societal impact of smoking-related diseases is inequitably distributed with, for example, Aboriginal and Torres Strait Islander peoples experiencing around five times greater CVD burden than other Australians.(3)

Mobile health (mHealth) is a term used for the practice of medicine and public health supported by mobile devices. It is a multidimensional field encompassing a wide variety of tools, technologies, and models of health care delivery. A systematic review of clinical trials to reduce smoking rates in Indigenous populations, conducted in 2013, analysed five studies- three testing Quitline protocols combined with cessation products compared with Quitline alone, and two using culturally adapted cessation counseling using mobile phones.(4) Outcomes were mixed, however, a New Zealand trial involving 1705 participants (355 Māori) found a greater than two-fold increase in smoking abstinence at 6 weeks (28% vs. 13%) which appeared to be sustained at 6 months.(5) Importantly, abstinence rates were equally successful amongst Māori as non-Māori in the intervention arm.(6) This program is now being administered via NZ Quitline. The Txt2Stop trial adapted the NZ program for the United Kingdom. The study involving 5,800 participants across the UK, also demonstrated a doubling of quit rates over the control group at six months (verified abstinence of 10.7% v.4.9%).(7) The program has since been shown to be highly cost-effective and has been adopted by the National Health Service. A recent Cochrane systematic review found mobile phone-based smoking cessation interventions led to a 71% increased rate of smoking cessation when compared with control with the results largely driven by the outcomes in the NZ and UK trials.(8) There have not been any controlled trials of mHealth interventions for smoking cessation in Australia to date.

#### 3.2 Intervention development

Our work on developing an mHealth intervention to assist Aboriginal and Torres Strait Islander smokers in abstaining from smoking was conducted in three phases:

**1. Landscape analysis:** A review of existing smoking cessation support services, products and research involving Aboriginal and Torres Strait Islander people with a specific focus on people living in NSW was conducted. The ATRAC Framework – A Strategic Framework for Aboriginal Tobacco Resistance and Control in NSW, which forms the blueprint for policy in NSW was also reviewed. In parallel with this review a competitor analysis of national and international mobile applications that have been used for smoking cessation was conducted.

**2. User centred app design:** An expert user group involving current smokers and ex-smokers from Aboriginal Community Controlled Health Services was convened to guide intervention development. A series of interactive sessions were conducted with this user group in which user experience, attitudes toward existing smoking cessation services and mobile applications were canvassed. From this a series of hypothetical user personas were developed. This enabled a deep contextual understanding of user experiences, knowledge, attitudes, behaviour related to both tobacco use and

use of mobile technology, triggers for behaviour change and past experiences with quitting and cessation maintenance. Following this, a series of rapid visualisation design cycles were conducted to develop and refine app development until the final software specification was agreed on.

In parallel with this process the existing bank of motivational text messages was adapted in consultation with user groups to ensure they were appropriate for use in this setting.

**3. Software development:** Once the software specification was finalised the development phase commenced. An existing text-message bank which has been used in previous studies was adapted following previously used methodology to enhance applicability and acceptability to the target population. This involved user feedback and focus group testing of these with Aboriginal community members in collaboration with existing ACCHS partners. The existing text messages were modified accordingly and a series of new messages were added to the database.

### 3.3 Objectives

The overall project goal is to develop and evaluate an mHealth intervention to assist Aboriginal people in NSW with smoking cessation assistance. We hypothesise that a multi-faceted smoking cessation mobile application (Can'tEvenQuit), provided as part of routine smoking cessation services, will result in a doubling of biochemically verified smoking abstinence rates at 6 months when compared with usual care.

### 3.4 Trial/study Design

The Can't Even Quit trial will be evaluated using a single-blind randomised controlled trial involving 200 regular health service attendees who are current tobacco smokers

## 4. Methods

### 4.1 Study Setting

Three study settings will be used to recruit interested participants:

- Aboriginal Community Controlled Health Services
- Aboriginal Quitline
- Agency for Clinical Innovation – 1 Deadly Step program

### 4.2 Eligibility Criteria

Participants will be eligible if they are able to give informed consent and meet all of the following criteria:

- Current smokers aged 16 years or older
- Self-identification as an Aboriginal and/or Torres Strait Islander person
- Willing to make an attempt to quit smoking in the next month
- Access to an iPhone or Android smartphone

### 4.3 Intervention arm

All participants will be free to participate in any other smoking cessation service or support that they wish to use, and will be offered Quitline and local ACCHS contact numbers. Participants allocated to the intervention group will have the opportunity to download and register using the Can'tEvenQuit app immediately. The app will be accessible via the Apple App Store and Google Play. Intervention

arm participants will be able to invite external people to use a simplified version of the app to support participation in a quit smoking challenge.

A support worker will facilitate with registration profile, password set-up and establishing a tailored quit plan. Participants will then be given a tutorial of app feature including how to set up a challenge, motivational support and tracking progress on their plan. App set up can also be done without the use of a support worker if desired. Detailed information about the intervention content, design and features are provided in Appendix 1.

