#### 4.4 Control arm

Participants in the control arm will continue with their usual health care. They will be encouraged to take advantage of all available smoking cessation support services offered either through the ACCHS or through Quitline. Although participants in the control group could potentially download the app, they will be unable to successfully register to use it (via a database cross-check). At the end of 6 months follow-up control arm participants will be offered access to the app should they be interested in using it for a minimum 6-month period.

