#### 4.6 Sample size

On the basis of the Text2Quit and Text2Stop trials we estimate the control arm abstinence rate at 6 months to be 5%. Assuming that the abstinence rate is double that of the control arm, we calculate that 1000 participants would be needed to detect a 5% absolute difference (ie: 10.0% vs 5.0%; relative risk 2.00), assuming a 15% loss to follow-up,  $\alpha=0.05$  and 80% probability of detecting a significant difference with p values  $<0.05$  judged as significant. This study will be a pilot RCT in which 200 participants will be recruited to assess feasibility, resource considerations, acceptability and preliminary effectiveness data to inform a future, adequately powered trial.

Using the secondary outcome measure of 7-day abstinence rates at 4 weeks, and assuming the control arm abstinence rate is 12% and the intervention arm abstinence rate is 2.4 times greater (as observed in the Text2Stop trial), there will be 80% probability of detecting a significant difference with 200 participants from the pilot study under the same assumptions as above.

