#### 4.7 Recruitment

Recruitment will take place via three settings. Up to four Aboriginal Community Controlled Health Services will be invited to participate in the study. Callers to the Aboriginal Quitline and community members screened at a 1 Deadly Step event will also be invited to participate. Interested individuals will be contacted by the project manager to discuss participation.

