#### 4.8 Allocation

Randomisation will be single blinded and conducted through the George Institute's central, computer-based randomisation service. Allocation will be 1:1 intervention versus control using a minimisation algorithm to balance for sex, age and Fagerstrom score for nicotine dependence. Staff involved in data collection and analysis will be blinded to treatment allocation.

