## 5. My Challenges

- Challenge others and compete. A simple workflow has been designed to enable others to join a challenge.
- Participants will be able to drag and drop people into their “circle” to invite them to a challenge. They can set the challenge type, date and duration.
- Receivers of a challenge will receive a pop-up or push notification or SMS message inviting them to the challenge. They will be able to view who has challenged them, view others who are taking part and decide to participate now or next time. For new participants instructions will be given on how to set up the app to participate in the challenge. A challenge can be issued to anyone, however, participants in the control arm of the trial will be prevented from being invited into a challenge.
- Once a challenge is set participants will be able to view the progress of others attempting the same challenge, whether they “craved and caved” on the challenge and view and share their progress with others via standard social media platforms like Facebook.

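### A smoker who already uses the simplified app as an invited challenger can later be enrolled and allocated to control, because eligibility does not screen for earlier app use and the safeguards cover only people already in the control arm

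*Protocol*

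**What the plan says.** The protocol opens the app to people outside the trial. Under section 4.3, intervention "arm participants will be able to invite external people to use a simplified version of the app", in support of a quit-smoking challenge. Appendix 1 (My Challenges) sets the reach and its one limit: "A challenge can be issued to anyone, however, participants in the control arm of the trial will be prevented" from being invited. It adds: "For new participants instructions will be given on how to set up the app to participate in the challenge".

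Section 4.4 (Control arm) gives the other safeguard. Control participants might download the app, but "they will be unable to successfully register to use it (via a database cross-check".

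Section 4.2 opens with "Participants will be eligible if they are able to give informed consent and meet all of the following criteria" and lists four: current smoker aged 16 or over, Aboriginal and/or Torres Strait Islander identity, willingness to try to quit within a month, and access to a suitable phone. There is no exclusion list and nothing on present or past use of the app.

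On recruitment, section 4.7 says "Up to four Aboriginal Community Controlled Health Services will be invited to participate in the study", and adds Aboriginal Quitline callers and people screened at 1 Deadly Step events. On allocation, section 4.8 says "Allocation will be 1:1 intervention versus control using a minimisation algorithm to balance for sex, age and Fagerstrom score for nicotine dependence". The synopsis names study centre, gender and age instead. Neither account includes earlier app use.

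**The concern.** The protocol means to keep the control arm off the app and has two barriers for that purpose. Both are worded for someone who is already a control. Intervention participants may register immediately after allocation, so invitations can circulate while recruitment continues. A smoker invited in that period can set up the simplified version and then come forward through one of the recruitment settings. That person meets all four criteria and has an even chance of being allocated to control.

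Two things are at stake. Controls who have gained something from the app raise the control abstinence rate and shrink the estimated effect. Intervention participants who already know the app make its uptake and usage figures harder to read. Feasibility, acceptability and preliminary effectiveness are what this pilot is meant to supply for a larger trial (section 4.6), so either distortion could carry into that trial's design.

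**Working it through.** **Step 1. Which orders of events are covered?**

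| Order of events | What the protocol provides |
|---|---|
| Allocated to control, then tries to register | Blocked by the database cross-check (4.4 Control arm) |
| Allocated to control, then is invited to a challenge | Blocked (Appendix 1, My Challenges) |
| Invited and registered, then screened and allocated to control | Not screened out (4.2) and not balanced (4.8). New invitations are blocked after allocation; the existing account is not addressed |

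The third row is the gap.

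**Step 2. Reproduce the plan's own power figure.** The inputs are from section 4.6: 7-day abstinence at 4 weeks, 12% in control, 2.4 times that in intervention (0.12 × 2.4 = 0.288), 200 participants, 15% loss and α = 0.05. Section 4.11 makes the test two-sided. Evaluable: 200 × 0.85 = 170, or 85 per arm.

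Power = Φ{[(p₂ − p₁)√n − 1.96√(2p̄(1 − p̄))] / √(p₁(1 − p₁) + p₂(1 − p₂))}, where p̄ is the mean of p₁ and p₂.

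With p₁ = 0.12, p₂ = 0.288 and n = 85: p̄ = 0.204, and the numerator is 0.168 × 9.220 − 1.96 × 0.570 = 1.549 − 1.117 = 0.432. The denominator is 0.557. Power = Φ(0.775) = 78.1%, against 80% stated. The stated figure is reproduced to within 2 points and is not in dispute.

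**Step 3. Dilution.** Let c be the share of controls exposed before enrolment and e the fraction of the app's assumed effect that they gain. Both are assumptions.

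Control rate = 0.12 + c × e × (0.288 − 0.12) = 0.12 + c × e × 0.168

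Example, c = 10% and e = 1: 0.12 + 0.0168 = 0.1368. The apparent relative risk is 0.288/0.1368 = 2.11, and power at 85 per arm is 67.6%.

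| c | e | Control rate | Apparent RR | Power, 85 per arm |
|---|---|---|---|---|
| 0 | – | 12.00% | 2.40 | 78.1% |
| 5% | 1 | 12.84% | 2.24 | 73.1% |
| 10% | 1 | 13.68% | 2.11 | 67.6% |
| 20% | 1 | 15.36% | 1.88 | 56.1% |
| 5% | 0.5 | 12.42% | 2.32 | 75.6% |
| 10% | 0.5 | 12.84% | 2.24 | 73.1% |
| 20% | 0.5 | 13.68% | 2.11 | 67.6% |

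The intervention rate is held at 28.8% throughout.

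**Step 4. What the shares mean in people.** This exposure precedes randomisation, so it should fall on both arms about equally. Shares of 5%, 10% and 20% then correspond to about 0.05 × 200 = 10, 0.10 × 200 = 20 and 0.20 × 200 = 40 enrolees who were already app users. All would have been invited by at most about 100 intervention participants, some of whom enrol too late to have invited them.

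**The case against.** The strongest reply is that this is a narrow timing gap in a 200-person pilot that already guards against contamination in two ways. Much of the reply concerns size, and most of that stands:

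- Section 4.3 gives invitees only a simplified version. Nothing says that they receive the quit plan, the tutorial or the motivational messages.
- Challenges have a set date and duration, so exposure through one challenge may be short. Once a person is in the control arm, further invitations are blocked.
- Enrolees must still be current smokers. Someone who used the app and still smokes has not stopped on that exposure and is unlikely to gain the full assumed effect from randomisation onward.
- Challenges can go to anyone, including non-smokers and people far from the sites, and Quitline callers are not a closed local pool. That invitees overlap with recruits is a reasonable inference from the setting, but it is not documented.

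A reader might infer that intervention participants can hand the intervention itself to controls, or that nothing limits exposure once a pre-exposed person becomes a control. The documents do not support either. The invited version is reduced, the invitation block applies after allocation, and whether an existing account survives allocation is simply not stated.

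These points limit how large the effect could be. They do not close the gap: no provision identifies an invited user at screening. Eligibility is also a matter for the protocol, not something normally left to an analysis plan.

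**Conclusion.** The gap is real, of unknown size and cheap to close. No stated figure is wrong and no two passages contradict each other on this point. The fault is that the protections miss one order of events.

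For controls who benefit, the bias is toward no difference. The loss of power to 73%, 68% or 56% should be read as an upper bound for each assumed share, since it credits every exposed control with the app's full effect. The half-effect figures of 76%, 73% and 68% allow for the simplified version but are still illustrative. A reader might take 56% as a forecast. It is not: it needs one control in five to have been an app user already, and the documents give no count of external users to support that or any other share. That exposure would rise as recruitment proceeds is plausible, but it too is not stated.

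The change should be made before recruitment, with medium confidence that the route would matter in practice.

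**What to change.** 1. Add an exclusion to section 4.2 for anyone who has already registered for any version of the app, including as an invited challenge participant.
2. Check it at screening by a direct question, and by the database cross-check where invited users are held in that database. The protocol does not say whether they are, or which identifiers the check uses, so this needs confirming.
3. Record any matches found after enrolment, by arm, as a measure of contamination. Those participants stay in the intention-to-treat analysis.
4. State in section 4.4 (Control arm) how the cross-check applies to an account that existed before allocation. What should happen to such an account is for the investigators to decide.

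The cost is one eligibility line, one screening question, a database query if invited users are held there, and the loss of a few otherwise eligible people. If that loss is judged too great, recording earlier app use at baseline would at least make the problem measurable.
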